Investigation of risk factors for onset and relapse of Crohn's disease based on insurance claims database.

Vice Director and Associate [name]

Affiliation: Kitasato Research Institute Hospital, Kitasato University

Department: Center for Advanced IBD Research and Treatment

Address [name]

[contact]

[contact]

E-mail [contact]

1

October 9, 2020 Plan, Version 3

1. Objectives of clinical research

In this study, target patients will be extracted from the claims database and their clinical information will be extracted. Examine risk factors for Crohn's disease and relapse. To assess the validity of the inclusion criteria, a medical record review will be performed on some of the extracted cases to evaluate the positive or negative predictive value of the inclusion criteria.

2. Patients

2.1 Inclusion criteria

Extract the following patients from the database held by JMDC Corporation.

① Patients diagnosed with CD using ICD-10 coding of K50 (Appendix 1).

② Patients diagnosed with CD using the ICD-10 coding of K50 (Appendix 1).

In addition to (1) and (2) above, patients who, within ±12 months from the date of diagnosis, have prescribe code or procedure code listed in the national guidelines for Crohn's disease. (Reference 1)

③Patients who do not meet the above criteria.

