2.2 Exclusion Criteria

There are no exclusion criteria for this study.

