4.1 The designs of clinical research

A case-control study conducted with JMDC co, Ltd,.

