4.4 Case Registration Method

Extract the following information about the target case.

1) Date of diagnosis of Crohn's disease

2) Patient background (gender, age, height, weight, medical history, family history, current medications, and (Crohn's disease, time of onset (disease duration), disease type)

3) Presence or absence of complications such as anal lesions, stenosis, fistula, skin, arthritis, etc.

4) Lifestyle factors such as alcohol consumption and smoking habits before the onset of Crohn's disease

5) Lifestyle factors such as alcohol consumption and smoking habits after the onset of Crohn's disease

6) Therapeutic drugs (mesalazine, steroids,

immunomodulators, biologics) (Drugs listed in the diagnostic criteria and treatment guidelines for Crohn's disease*1 such as

(7) NSAIDs, antibacterials, statins, oral contraceptives, and other drugs related to the onset and relapse of Crohn's disease. History of use of the drug to be given

8) Availability and date of surgery

9) Hospitalization and date

10) Presence and date of malignancy in and outside the intestinal tract 5. evaluation items

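### A prescription up to 12 months before diagnosis can complete the treatment-code criterion, so if that criterion defines cases, the onset odds ratio of any studied drug class also on the guideline list can be inflated

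*Protocol*

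**What the plan says.** Protocol section 2.1 gives a code-only criterion, "① Patients diagnosed with CD using ICD-10 coding of K50 (Appendix 1", and prints criterion ② in the same words. A treatment-code sentence follows, opening "In addition to (1) and (2) above, patients who" and requiring a code "within ±12 months from the date of diagnosis, have prescribe code or procedure code listed in the national guidelines". The qualifying list is not printed; it is left to Reference 1. The only comparison group described is "③Patients who do not meet the above criteria". Section 2.2 adds "There are no exclusion criteria for this study".

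Section 4.4 collects drugs under two items. Item 6 covers therapeutic drugs and names mesalazine, steroids, immunomodulators and biologics, with an open-ended reference to the guideline: "Drugs listed in the diagnostic criteria and treatment guidelines for Crohn's disease*1 such as". Item (7) covers the history of use of "NSAIDs, antibacterials, statins, oral contraceptives, and other drugs related to the onset and relapse of Crohn's disease".

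Section 4.1 calls the design "A case-control study conducted with JMDC co, Ltd". The primary endpoint in section 5.1 is risk factors for onset and relapse, and section 9 lists logistic regression as the multivariate method.

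**The concern.** The treatment-code window is symmetric around diagnosis, so it takes in the year in which an onset exposure would naturally be looked for. Suppose a class is both a qualifying drug and a studied exposure. A K50 patient with no other qualifying code is then a case if that drug was prescribed in the year before diagnosis, and is not a case without it. Controls meet no matching condition. Part of any association between that class and onset would come from the case definition and not from the disease.

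The planned validation would not show this. Section 4.2 has a physician judge from the chart whether the patient had Crohn's disease. A true Crohn's patient who was selected through such a prescription counts as a true positive, so a high positive predictive value could stand beside a distorted odds ratio.

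**Working it through.** The protocol gives no figure on this point, so there is none to reproduce. The size follows from selection algebra.

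**Inputs**
- From the documents: K50 is always required; the code window is 12 months either side of diagnosis (2.1); the design is case-control (4.1) with logistic regression (9).
- Assumed, because the documents do not give them:
  - The treatment-code criterion defines cases.
  - The studied class is a qualifying drug.
  - p is the exposure prevalence, equal in K50 patients and controls (no true effect).
  - r is the share of unexposed K50 patients who qualify through another code.
  - s is the share of exposed patients whose counted exposure falls in the 12-month look-back.
  - Exposed patients outside the look-back qualify at the same rate r as unexposed patients.

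**Formula**
- Chance of qualifying if unexposed: r.
- Chance of qualifying if exposed: s + (1 − s)r.
- Exposure odds among qualifying cases: p[s + (1 − s)r] / [(1 − p)r].
- Exposure odds among controls: p / (1 − p).
- Ratio: [s + (1 − s)r] / r = 1 + s(1 − r)/r. The prevalence p cancels. With a true effect, the true odds ratio is multiplied by this factor.

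**Example.** Take 1,000 K50 patients with p = 0.2 and r = 0.8. At s = 1, all 200 exposed patients qualify, as do 0.8 × 800 = 640 unexposed. The case odds are 200/640 = 0.3125 and the control odds 0.2/0.8 = 0.25, so the odds ratio is 1.25. At s = 0.5, 100 + 0.8 × 100 = 180 exposed patients qualify; the case odds are 180/640 = 0.28125 and the odds ratio is 1.125.

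**Observed odds ratio when the true value is 1**

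| r | s = 1 (upper bound, 1/r) | s = 0.5 | s = 0 |
|---|---|---|---|
| 0.95 | 1.05 | 1.03 | 1.00 |
| 0.90 | 1.11 | 1.06 | 1.00 |
| 0.80 | 1.25 | 1.13 | 1.00 |
| 0.70 | 1.43 | 1.21 | 1.00 |
| 0.50 | 2.00 | 1.50 | 1.00 |

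A simulation with s = 1 used 2 million K50 patients and 2 million controls per setting, p = 0.05, 0.2 and 0.4, and r = 0.95, 0.8 and 0.5. Under the treatment-code criterion the odds ratio came within about 0.01 of 1/r. With K50 alone as the case definition it lay between 0.997 and 1.008, that is, no inflation.

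**The case against.** The strongest reply is that the overlap cannot be seen in the documents. No class is named both as a guideline drug and as an onset factor, and items 6 and (7) of section 4.4 list different classes. A reader might infer that the antibacterial odds ratio is inflated. The protocol does not support that: antibacterials appear only under item (7), and whether the guideline lists them cannot be checked here. This stands, and it makes the point conditional. It does not remove it, because item (7) ends in an open category, the qualifying list is left to an outside source, and nothing in 2.1 keeps the two apart.

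Second, K50 alone may define the cases. Section 9 includes all enrolled patients, and the expected number is the total of Crohn's disease cases in the database. Under the code-only criterion, or the union of both criteria, the prescription selects nobody and the factor is 1.00. This also stands. However, ① and ② are printed alike and the treatment-code sentence refers to both, so the text does not settle which reading applies. A reader might also infer that a prescription by itself makes a patient a case. It does not, since a K50 code is always needed.

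Third, 1/r is an upper bound. It would be too strong to say that lagging the exposure cannot help. Counting only exposure before the 12-month look-back removes the direct mechanism, and what remains is carry-over from persistent users whose earlier use predicts use in the window. Exposure windows and lags may be set in an analysis plan not shown here, so their absence is not criticised.

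Fourth, if few K50 patients qualify only through an overlapping drug, r is likely to be near 1 and the inflation small. That is fair, and it is why the larger values in the table should not be read as expected.

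**Conclusion.** The point holds in conditional form. As written, the window lets a pre-diagnosis prescription complete the treatment-code criterion, and nothing prevents a studied class from doing so. An onset odds ratio can be inflated if two things are true: that criterion defines the cases in the risk-factor analysis, and the class is on the guideline list. The protocol establishes neither.

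Where both hold, the factor is at most 1/r, reached only when all counted exposure lies in the look-back, and half that excess when half of it does. There is no inflation if K50 alone defines cases, or if counted exposure lies wholly before the look-back and does not predict use within it. The documents give neither r nor s, so no single value can be claimed. The correction is worth making because it bears on the primary endpoint, is cheap, and removes no one from the case group if there is no overlap.

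**What to change.** In section 2.1, state which criterion defines cases for the risk-factor analysis, and that no class analysed under section 4.4 item (7) can by itself satisfy the treatment-code criterion. Use the same qualifying list in the validation sample.

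Version 3 is dated October 9, 2020, after the stated end of case accumulation on September 30, 2020, so extraction may already be done. In that case, apply the rule at analysis by ignoring codes of the overlapping classes when assigning case status; this needs the qualifying codes to have been kept. For any overlapping class, also repeat the onset analysis with K50 alone as the case definition.

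The cost is a sentence or two, a comparison of two code lists, and one further analysis per overlapping class. K50 patients whose only qualifying code is an overlapping drug, probably few, drop out of the treatment-code criterion. The K50-alone analysis may have a lower positive predictive value, so it should be read beside the main result and not in place of it.

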2.2 Exclusion Criteria

There are no exclusion criteria for this study.

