7.2 Stopping the research itself

When the principal investigator decides that the research should be discontinued.

In the above cases, report to the hospital director and the Kitasato Research Institute Hospital Research Ethics Committee.

8. expected adverse events and emergency reporting methods In this study, we extracted and analyzed anonymized information from the medical fee database.

This is a study without medical intervention. No expected adverse events are expected.

9. analysis method

(1) Analysis target

All enrolled patients will be included in the analysis.

(2) Statistical analysis

Perform statistical analysis using the following methods, as appropriate.

Contingency table analysis: χ-square test, Fisher's exact test Comparison of two unpaired groups: unpaired t-test, Mann-Whitney U test.

Correspondence between two groups: Correspondence t-test, Wilcoxon sign rank test.

Survival time analysis: Cox regression analysis, Log-rank test Multivariate analysis: Logistic Regression Analysis

(indicating an approximate quote or vague suggestion) or something.

(3) Person responsible for analysis

[name], Deputy Director, Center for Advanced Inflammatory

7

Bowel Disease, Kitasato Institute Hospital, Kitasato University

(4) Evaluation of analysis results

The results of the analysis will be published after evaluation by the Center for Advanced Therapy of Inflammatory Bowel Disease.

10. expected research period

Case accumulation period: After approval by the director of the institution - September 30, 2020 (A.D.)

Validity evaluation period: After approval by the director of the institution - September 30, 2020 (A.D.)

Case analysis period: After approval by the director of the institution - March 31, 2021 (A.D.)

The number of cases to be studied and the basis for setting the number (1) Number of cases to be studied The expected number of cases is the total number of Crohn's disease cases recorded in the JMDC database target.

The number of cases required for validity assessment is 100 cases for criteria (1) and (2), and 200 cases for (3). (2) The basis for setting if the positive predictive value is set at 80% (95% confidence interval ± 0.1), the sample size required for validity assessment is 100 cases or criteria (1) and (2), and 200 cases for (3).

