 Appendix 1 ICD-10 codes used for extraction criteria K50.0 Crohn's disease of small intestine

 Crohn's disease of the ileum

 Crohn's disease of the jejunum

 Crohn's disease of the duodenum

 Crohn's disease of the small intestine

K50.1 Crohn's disease of large intestine

 Crohn's disease of the colon

 Crohn's disease of the appendix

 Crohn's disease of the rectum

K50.8 Other Crohn's disease

 Gastric Crohn's disease

 Gastroduodenal Crohn's Disease

 Crohn's disease of the anus

 Crohn's disease of small and large intestine K50.9 Crohn's disease, details unknown.   Crohn's disease

 Crohn's Juvenile Arthritis

 Steroid-Dependent Crohn's Disease

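### The onset analysis has no incident-case restriction and drug history is not limited to before onset, so established cases can enter and post-onset drug use can look like a risk factor

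*Protocol*

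**What the plan says.** - **Endpoint and design.** Section 5.1 combines risk factors for development and for relapse in one primary endpoint. Section 4.1 calls the study case-control.
- **Selection.** Section 2.2: "There are no exclusion criteria for this study". Section 2.1 admits any K50 patient ("Patients diagnosed with CD using ICD-10 coding of K50 (Appendix 1"). A further criterion adds a guideline treatment or procedure code "within ±12 months from the date of diagnosis".
- **Analysis set.** Section 9(1): "All enrolled patients will be included in the analysis".
- **Number of cases.** The paragraph after section 10: "The expected number of cases is the total number of Crohn's disease cases recorded in the JMDC database target". Section 4.2 puts the extraction at about 4,000, from a cumulative population of about 5.6 million, with data since 2005.
- **Exposures (section 4.4).** Item 1 is the date of diagnosis, and item 2 includes time of onset and disease duration. Item 4 is "Lifestyle factors such as alcohol consumption and smoking habits before the onset of Crohn's disease", and item 5 is its post-onset counterpart. Item 7 (NSAIDs, antibacterials, statins, oral contraceptives and other drugs related to onset and relapse) asks for history of use, with no division at onset.

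The protocol sets no look-back, minimum enrolment, incident subset or index date for the onset analysis.

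**The concern.** A case-control analysis of onset needs cases whose disease is new and exposures that precede it. A claims database also contains people who were already ill when their insurer's data began or when they joined. Their first K50 record may fall long after true onset. If they are analysed with the new cases, and their drug history is taken from whatever claims exist, the comparison mixes causes of the disease with its consequences.

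The item 7 drugs are where this matters most. Antibacterials or NSAIDs prescribed for early symptoms, for the work-up, or after diagnosis would be associated with being a case without having caused anything. The error is systematic, so a larger sample does not reduce it, and none of the tests or regressions listed in section 9(2) removes it. At stake is the validity of the onset half of the primary endpoint, chiefly for drugs.

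**Working it through.** The protocol gives no figure that depends on this point, so there is none to reproduce. The check compares the rules and then illustrates the size.

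**Step 1: who can enter.** Sections 2.1, 2.2 and 9(1) and the case-number paragraph all point the same way: every recorded case, new or established, is selected and analysed. The ±12-month window supports the diagnosis. It does not show that the diagnosis is new, and it accepts treatment codes from before the diagnosis date. Appendix 1 includes "Steroid-Dependent Crohn's Disease", a label that describes disease already under treatment. Neither of these creates the problem, because a K50 code alone is enough for entry, but neither screens out established disease. The expected yield is 4,000 / 5,600,000 = 71 per 100,000 of the cumulative population. That counts all recorded cases, and the incident share cannot be derived from it.

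**Step 2: which exposures are timed.** Lifestyle is split at onset (items 4 and 5). Item 7 is not. Items 1 and 2 collect diagnosis and onset dates, but no rule uses them to select cases or to limit drug exposure.

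**Step 3: what can be observed.** For a patient already ill on entering the database, drug use before onset lies outside the claims record. Splitting item 7 alone would not recover it; case selection has to change as well.

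**Step 4: illustration.** All inputs here are assumptions. Let p0 be exposure in controls and in new cases (no true effect), p1 the recorded exposure in established cases, and f the share of cases that are established:

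pc = (1 − f)·p0 + f·p1

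OR = [pc/(1 − pc)] / [p0/(1 − p0)]

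Example: p0 = 0.20, p1 = 0.40, f = 0.50 gives pc = 0.30 and OR = (0.30/0.70)/(0.20/0.80) = 0.4286/0.25 = 1.71.

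| f | p0 20%, p1 30% | p0 20%, p1 40% | p0 10%, p1 30% |
|---|---|---|---|
| 10% | 1.06 | 1.13 | 1.23 |
| 25% | 1.16 | 1.33 | 1.59 |
| 50% | 1.33 | 1.71 | 2.25 |
| 75% | 1.52 | 2.15 | 3.00 |

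The model assumes that exposure in every established case is measured after onset. If a drug is used less after diagnosis (p1 < p0), the same formula gives an odds ratio below 1, a spurious protective effect.

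**Step 5: would it reach significance?** Assume 4,000 cases and 4,000 controls (the number of controls is not in the protocol), and take z as the difference over its pooled standard error.
- 22% v 20% (OR 1.13): 0.02 / √(2 × 0.21 × 0.79 / 4,000) = 0.02 / 0.00911 ≈ 2.2.
- 21% v 20% (OR 1.06): 0.01 / √(2 × 0.205 × 0.795 / 4,000) = 0.01 / 0.00903 ≈ 1.1.

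A modest bias can thus pass as a finding, but the smallest one shown would not.

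**The case against.** The best defence is that the protocol leaves the matter open. Index date, look-back and endpoint-specific analysis sets commonly belong in a statistical analysis plan, which is not shown here. One broad extraction serves onset, relapse and the validity assessment, and established cases are legitimate for relapse. The rule that all enrolled patients are analysed does not say in so many words that each one enters the onset model. Section 4.4 also collects time of onset, with which new and established disease could be separated.

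Part of this stands. A reader might infer that the plan treats the first K50 record as onset and counts every case as new. The protocol says neither; it leaves the index date undefined. A reader might also infer that all post-onset exposures are counted as risk factors for onset. Items 4 and 5 contradict that for lifestyle, so the untimed exposure is the drug history.

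What does not stand is that this is only missing detail. The protocol affirmatively states no exclusions, an analysis set of all enrolled patients, and a case number equal to all recorded cases. Followed as written, those rules put established disease into the onset analysis. A later plan that restricted onset cases would sit at odds with them, and section 19 requires ethics committee approval for protocol changes. Collecting time of onset helps only if some rule uses it.

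**Conclusion.** The point holds as a design weakness in the onset half of the primary endpoint. As written, the selection and analysis rules admit established cases, and item 7 drug history is not confined to the period before onset, so reverse causation is possible for drugs. For patients already ill on entering the database, pre-onset exposure may not be observable in the claims at all.

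The actual size is unknown: the established share and the exposure frequencies are not in the document. Under the assumed 20% control exposure and 30–40% exposure after onset, the spurious odds ratio is 1.06–1.13 with 10% established cases and 1.33–1.71 with 50%. It would be wrong to say that the bias must become statistically significant with 4,000 cases, as the lowest scenario shows. The relapse analysis is not affected by this point.

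**What to change.** Amend sections 2.2 and 9(1), for the onset analysis only:

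1. Restrict cases to those whose first K50 code follows a stated minimum period of continuous enrolment with no K50 code (for example 12 months, with a longer period as a sensitivity analysis). Since a first code has none before it by definition, the enrolment length does the work.
2. Take that first K50 code as the index date. Exclude patients with Crohn's-specific treatment codes in the look-back, or test their exclusion in a sensitivity analysis. Non-specific drugs such as steroids should not set the index date, because a course for another condition would misdate onset.
3. Apply the same enrolment requirement to controls and assign them an index date.
4. Count item 7 drug exposure only before the index date, with a lag (for example 6 months) and a no-lag sensitivity analysis.
5. Keep all cases for the relapse analysis.

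The 12- and 6-month figures are examples with no basis in the protocol; the study team should choose and justify them. The cost is a protocol amendment with ethics committee approval, a filter on enrolment dates (assumed to be available in the database), and fewer onset cases than about 4,000.

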 2.3 Patients for inclusion criteria validity assessment

Patients who visited Kitasato University Kitasato Institute Hospital from May 1, 2012, to March 31, 2019, and meet the following criteria will be eligible.

(1) 100 cases each of patients who meet the inclusion criteria ① and ②

(2) 200 cases of patients who meet ③

3. Informed consent

Since this research uses receipt data and medical records, no written explanation or consent will be obtained by the "Ethical Guidelines for Medical and Health Research Involving Human Subjects”. By this guideline, informed consent was obtained in the form of opt-put on the web-site. In this way, patients or surrogates patients who refuse to participate in the study will be removed from the analysis and immediately disposed of.

4. Methods of clinical research

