4.2 Procedure

This study was conducted in collaboration with JMDC Corporation, a company whose main business is to provide medical statistics data services by maintaining receipts (inpatient, outpatient, and dispensing) and medical examination data from multiple health insurance associations.

The data has been accumulated since 2005, and the cumulative population is approximately 5.6 million as of June 2018. About 4,000 target cases are extracted from the database (anonymized processed information) held by JMDC, using extraction criteria. JMDC will construct analysis data from the clinical information, and conduct statistical analysis of the onset and relapse factors of Crohn's disease from the constructed analysis data.

A validity evaluation of the inclusion criteria will be also conducted. JMDC, Inc. will extract the 400 cases of patients in Kitasato University Kitasato Institute hospital to be used for the validity evaluation. JMDC will extract a total of 400 patients who meet and do not meet the criteria from the receipts held by the hospital, and anonymize them by assigning a research number to the research subject so that no specific individual can be identified at this facility (Correspondence table provided by [name], Personal Information Manager). The corresponding table will be kept in a locked cabinet by the principal investigator, and the information will not be taken outside the facility. Cases will be selected from the anonymized data according to the inclusion criteria, and random sampling will be conducted. A medical chart review to determine whether the cases had Crohn's disease was conducted by a research physician. Based on the results of the medical record review, the validity of the inclusion criteria will be assessed by calculating the positive/negative predictive value, sensitivity, and specificity.

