5.2 Secondary endpoints

The validity of the extraction conditions (positive predictive value, negative predictive value, sensitivity, specificity).Report on deviations from the implementation plan

The principal investigator must obtain prior approval from the Kitasato Research Institute Hospital Research Ethics Committee before implementing the clinical research protocol. Besides, it is prohibited to deviate from or change the in the event of any deviation from the clinical research protocol, the principal investigator shall notify the investigator of the deviation. (2) The researcher shall record all of the following information, along with the reasons for it, and report it to the Research Ethics Committee.

7. discontinuation and dropout criteria

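### The 200 charts from patients not meeting the criteria rest on a PPV target that this group cannot have; the precision of NPV is left unstated and sensitivity will have no usable precision

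*Protocol*

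**What the plan says.** Protocol 2.1 defines the comparison group as "③Patients who do not meet the above criteria", and 2.2 adds "There are no exclusion criteria for this study". The frame for the chart review (2.3) is one hospital over about seven years: "Patients who visited Kitasato University Kitasato Institute Hospital from May 1, 2012, to March 31, 2019, and meet the following criteria will be eligible". From it come "1) 100 cases each of patients who meet the inclusion criteria ① and ②" and "2) 200 cases of patients who meet ③". Section 4.2 fixes how they are drawn: "Cases will be selected from the anonymized data according to the inclusion criteria, and random sampling will be conducted".

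The secondary endpoint (5.2) is "The validity of the extraction conditions (positive predictive value, negative predictive value, sensitivity, specificity", and 4.2 names the same four measures. The paragraph on the number of cases, after section 10, gives one basis for all three groups: "if the positive predictive value is set at 80% (95% confidence interval ± 0.1". It concludes that 100 charts are needed for ① and ② and 200 for ③. No planning value or precision is given there for NPV, sensitivity or specificity.

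**The concern.** PPV is the share of true Crohn's disease among patients whom the criteria flag. Patients in ③ are not flagged and do not enter it. Their charts serve to show how many true cases the criteria miss, which drives NPV and sensitivity. A PPV target is therefore the wrong basis for that group.

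This matters because a random draw from hospital patients who fail the criteria will hold few or no true cases. The study could report an NPV close to 100%, and from a pooled table a sensitivity close to 100%, and readers would take both as proof that the criteria find nearly all cases. Criteria that miss many cases could easily give the same figures. The risk-factor analysis depends on case identification, so the validation result will carry weight.

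**Working it through.** **1. The plan's own figure.** For one proportion, n = z²p(1−p)/d². With p = 0.8 and d = 0.1: 1.96² × 0.16 / 0.01 = 61.5, so 62. Exact (Clopper-Pearson) limits need about 90. A figure near 100 comes out only at p = 0.5 (96.04, so 97), which is not the stated input. One hundred charts thus more than meet the PPV target for ① and ②: the half-width at 80% is 7.8 points. The 200 for ③ follows from none of these calculations.

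**2. Expected missed cases in 200 charts.** The share of true cases among criterion-negative patients is m = prev × (1 − sens) / (1 − prev × sens / PPV), with PPV = 0.8 from the protocol. The expected number is 200m, the chance of none is (1 − m)^200, and NPV = 1 − m. The database ratio uses the figures in 4.2: 4,000 / 5.6 million = 0.071%. The hospital's prevalence is not in the protocol, so 0.5% to 5% is an assumed range.

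| Prevalence | Sensitivity | Expected missed | Chance of none | NPV |
|---|---|---|---|---|
| 0.071% (database) | 0% | 0.14 | 87% | 99.93% |
| 0.071% (database) | 50% | 0.07 | 93% | 99.96% |
| 0.5% (assumed) | 95% | 0.05 | 95% | 99.97% |
| 1% (assumed) | 80% | 0.40 | 67% | 99.8% |
| 2% (assumed) | 50% | 2.0 | 13% | 99.0% |
| 5% (assumed) | 50% | 5.2 | 0.5% | 97.4% |
| 5% (assumed) | 95% | 0.5 | 59% | 99.7% |

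**3. What 200 charts give.** If none is a missed case, the exact two-sided 95% upper limit for the missed share is 1 − 0.025^(1/200) = 1.83%. This is a valid bound on 1 − NPV.

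**4. What that means for sensitivity.** Weighted to the hospital, sensitivity = TP / (TP + N₃ × x/200), where x is the number of missed cases found and N₃ the size of ③. Assume TP = 400 (500 flagged at PPV 80%) and N₃ = 50,000. Each missed case found then stands for 250 patients. The limits below put the exact limits of x/200 into the formula and treat TP as known.

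| x | Weighted sensitivity | 95% limits | Pooled, unweighted |
|---|---|---|---|
| 0 | 400/400 = 100% | from 30% | 160/160 = 100% |
| 1 | 400/650 = 62% | 23% to 98% | 160/161 = 99.4% |
| 2 | 400/900 = 44% | 18% to 87% | 160/162 = 98.8% |

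The pooled column takes 160 true positives among the 200 flagged charts (PPV 80%). Over assumed ranges of 20,000 to 200,000 patients in ③ and 500 to 2,000 flagged, the lower limit after 0/200 runs from 10% to 81%.

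**5. Specificity.** Pooling distorts this too. With PPV 80% and no missed cases, the 400 charts give 200/(200 + 40) = 83%. Weighted on the same assumed sizes it is 50,000/(50,000 + 100) = 99.8%.

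**The case against.** Four points on the other side deserve weight.

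- **NPV is estimated without bias.** A reader might infer that NPV carries no information. That is too strong: a random sample of ③ estimates NPV properly and 0/200 bounds it. If ③ supplies the controls, their contamination with true cases is a relevant quantity, and this sample answers it. What stands against NPV is only that a high value says little about how many cases are found.
- **The hospital is not the database.** It houses an IBD centre, so 0.071% may be far too low. At an assumed 5% and 50% sensitivity, 5.2 missed cases are expected and poor criteria would show. The claim that almost none will be found depends on prevalence.
- **The extent of ③ is unclear.** In 2.1 the wording of ① and ② is the same, and the treatment-code condition is attached to both. Read literally, ③ is everyone without K50. If it also holds K50 patients without a treatment code, it contains more true cases, though it may still consist mostly of unrelated patients.
- **Pooling is not prescribed.** A reader might infer that sensitivity will come out near 100% whatever is found. That applies only to an unweighted calculation. The protocol does not call for one, and a weighting rule may properly sit in an analysis plan. Its absence is not counted as an error here.

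None of these supplies a basis for the 200 charts or makes sensitivity precise.

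**Conclusion.** The stated sample-size basis is wrong for ③ as written. It cannot apply to patients who fail the criteria, and it leaves the precision of NPV and sensitivity unaddressed although both are promised. This needs no assumption.

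The consequence for the estimates is conditional. For assumed prevalence up to 5% and sensitivity of at least 50%, about five missed cases at most are expected and NPV is about 97% or higher, largely because the disease is rare. Sensitivity can be computed but not with usable precision: under the assumed hospital sizes, a single chart moves it by 38 points. The documents do not support saying that sensitivity cannot be estimated at all, or that NPV is uninformative. A secondary endpoint is affected; the point should be corrected but does not invalidate the study.

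**What to change.** In the paragraph on the number of cases, keep the PPV basis for ① and ② only. For ③, state the precision that 200 charts give: 0/200 bounds the missed share below 1.83% (exact, two-sided 95%). Then:

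- Clarify ① and ② so that ③ is unambiguous, and record how many hospital patients fall in each group.
- Compute sensitivity and specificity only after weighting by these sizes, with exact limits. Do not report them from the pooled 400 charts.
- State beside the result that a high NPV is not evidence that the criteria find most cases.

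Enlarging a simple random draw is not practical: at the database ratio and 50% sensitivity, a 95% chance of finding even one missed case needs about ln(0.05)/ln(1 − 0.000357) ≈ 8,400 charts. Oversampling patients in ③ with related bowel codes, or with guideline drug or procedure codes, is optional and not clearly better. If 150 charts came from an assumed list of 1,000 such patients and 50 from the other 49,000, 0/50 would bound the missed share in the remainder only below 7.1%. That is up to 3,485 patients, for a sensitivity bound of 400/3,885 = 10%, against 30% for 0/200. Any such design must carry the remainder's uncertainty into the interval.

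The cost is a count of each group and a weighted calculation, with no new charts. That matters because version 3 is dated after the planned end of the validity evaluation, and 4.2 describes the chart review in the past tense. The downside is that the reported sensitivity interval becomes much wider.
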